### Withdrawals

Participants may withdraw at any time without providing a reason. They may also choose to withdraw their data from the study. A participant will be considered to be withdrawn if they request to leave the trial or they are lost to follow-up. If allocated to the exercise group, participants will be considered as withdrawn if they no longer attend the supervised exercise sessions, and in the lifestyle physical activity group if they no longer monitor daily physical activity through the fitness application. Data from withdrawn participants will not be used; only data from participants who completed the intervention and baseline and post-intervention assessments will be used in analysis.

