**Methods/design:**

A feasibility, exploratory RCT will be conducted. Fifty-one pre-menopausal females will be randomly allocated between an exercise group (EG), a lifestyle physical activity group (LPAG) and a control group. Participants in the EG will undertake a 12-week supervised aerobic exercise programme. The LPAG will aim to increase daily physical activity and reduce sedentary behaviour for 12 weeks. The control group will not take part in any intervention. Primary outcomes are feasibility and acceptability of the intervention and procedures. Secondary outcomes are oxidised LDL, aerobic fitness, blood lipid profile, fasting glucose and insulin, testosterone and inflammatory markers.

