### Randomisation and masking

Participants will be randomised in equal numbers between a supervised exercise programme, a lifestyle physical activity group and a control group. This will be undertaken using a computerised randomisation programme (QuickCalcs, GraphPad Software, USA) by an experienced researcher who is not involved in the study assessments. Allocation will be placed in sequentially labelled opaque envelopes. Each envelope will be offered to the participants, in sequence, by the chief investigator, on completion of their baseline assessments. It is not possible to mask participants or research team to the allocated intervention. Outcome assessors will be blinded to group allocation for anthropometric and fitness measures, but blood assays will be carried out by the same member of the research team. This is because blood assays are not considered to be subjective and are unlikely to be affected by outcome assessor bias.

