### Lifestyle physical activity group

Participants randomized to the lifestyle physical activity group will attend CSES at Sheffield Hallam University for all the tests and measurements but will not take part in the structured exercise intervention. However, advice and information on how to increase physical activity will be provided using British Heart Foundation guidelines: ‘Get active, stay active’. This will be discussed during the informed consent consultation. Participants will be asked to monitor and track their daily physical activity using a smartphone fitness application. This will either be Google Fit or Apple Health, since these are the default fitness apps for Android and Apple phones and are often pre-installed. The research team will gain permission to access their recorded activity. Between the baseline measurements and those after 12 weeks, participants will receive regular telephone support, approximately once a week, to obtain information about their progress and provide advice as needed.

Participants in the control group will not undertake any intervention but will still receive standard care from their medical professional which may include general weight-loss advice. To improve adherence for the control group, the research team will offer all participants allocated to the group the opportunity to undertake supervised exercise sessions at the CSES after their successful completion of the trial.

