### Outcome measures

#### Feasibility outcomes

The primary outcomes for this study are acceptability and feasibility of procedures for recruitment, allocation, measurement, and retention for the intervention procedures. Recruitment rate will be calculated by dividing the number of women eligible and consenting by the recruitment period. Attrition rates will be established as discontinuation of the intervention and loss to follow-up measurement for both conditions. Compliance will be monitored by session attendance and monitoring the data from recorded daily physical activity, with examination of reasons for drop-out or non-compliance. Reasons for drop-out will also be used to assess the suitability of allocation procedures. Suitability of measurement procedures will be evaluated by completion rates and reasons for missing data. The post-intervention interview will be used to assess the acceptability of the exercise programme and lifestyle physical activity group intervention, along with attendance and compliance data.

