#### Secondary outcomes

Serum oxidised LDL is the secondary outcome of the current study and will be analysed by enzyme-linked immunosorbent assay (ELISA). Optical density will be measured using an electronic plate reader and can be used to determine the quantity of the specific antigen in the blood using a calibration curve.

ELISA will also be used for quantitative analysis of C-reactive protein, neopterin, TBARS, fasting insulin and sex hormone binding globulin (SHBG). Free testosterone will be measured using a liquid chromatography method. This method has been chosen due to its ability to detect small amounts of serum testosterone, particularly in lower concentrations in females [20]. Free testosterone will be quantified using a calibration curve and calculating peak area.

Aerobic fitness will be assessed using the Astrand-Rhyming test. This is a submaximal single-stage test performed on a cycle ergometer, lasting between 6 and 7 min [21]. The goal is to obtain heart-rate values between 125 and 170 beats per minute (bpm) for a given work-rate at 50 revs/minute (50 or 75 watts for unconditioned women) [21]. Heart rate is then measured at the fifth and sixth minute if steady state (a difference ≤ 5 bpm is achieved), and the average of the two heart-rate measurements can be used to estimate VO_2max_ according to a nomogram. This value must be adjusted for age to account for decreasing maximal oxygen uptake and maximal heart rate with age [19].

For lipid profile (including LDL-cholesterol, HDL-cholesterol, TG and TC) and fasting glucose, a Cholestech Automated Analyser will be used. A fingerprick blood sample is obtained and collected into a capillary tube. The sample is then inserted into the machine cassette. This produces an automated reading from the sample in which accuracy can be maintained by using control samples and calibrations. HDL sub-fractions will be measured using gel electrophoresis.

In order to measure the amount of lifestyle physical activity (and subsequent sedentary activity), the long-form International Physical Activity Questionnaire (IPAQ) will be administered at baseline and post-intervention to all participants. This will be used to compare differences in time spent sitting, both during the week and weekend, and the amount of lifestyle physical activity (including transport, housework, and leisure time) undertaken.

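### In the lifestyle arm the withdrawal rule turns on app logging, so attrition and the analysis set reflect self-monitoring rather than uptake of the intervention

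*Protocol article*

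**What the plan says.** The Abstract (Methods/design) sets the arm's purpose: "The LPAG will aim to increase daily physical activity and reduce sedentary behaviour for 12 weeks".

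Withdrawals in the protocol article gives two grounds that apply to every arm: "A participant will be considered to be withdrawn if they request to leave the trial or they are lost to follow-up". It then adds one ground for each active arm. In the exercise arm it is no longer attending supervised sessions. In the lifestyle arm a woman is withdrawn "in the lifestyle physical activity group if they no longer monitor daily physical activity through the fitness application". The control arm has no added ground. The section closes by restricting the analysis: "only data from participants who completed the intervention and baseline and post-intervention assessments will be used in analysis".

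Feasibility outcomes counts discontinuation of the intervention, together with loss to follow-up measurement, as attrition. It treats compliance as a separate item: "Compliance will be monitored by session attendance and monitoring the data from recorded daily physical activity". Data analysis names attrition and compliance among the critical parameters for the full-scale trial.

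Under Randomisation and masking, envelopes are offered "on completion of their baseline assessments". App tracking is described only under Lifestyle physical activity group, where Google Fit or Apple Health is chosen "since these are the default fitness apps for Android and Apple phones and are often pre-installed". Under Secondary outcomes, the long-form IPAQ "will be administered at baseline and post-intervention to all participants", to compare sitting time and lifestyle activity.

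**The concern.** Logging is a tool for self-monitoring. The intervention is the change in behaviour that the tool is meant to support. The rule takes the first as the sign that a woman is still in the second, and this can mislead in two directions.

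- A woman who logs for 12 weeks without changing her activity or sitting time is counted as retained.
- A woman who stops logging is counted as withdrawn, and her data are dropped, even if she has become more active and attends the post-intervention assessment.

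The first affects how the retention figure is read. The second also biases the comparison. Control women are lost only by asking to leave or by loss to follow-up, whereas lifestyle women can also be removed for behaviour after allocation. The lifestyle-versus-control contrast then sets women who kept logging against all assessed controls.

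Attrition is part of the primary outcome and feeds the design of the next trial. A team planning that trial could take high retention as evidence that the intervention was taken up, or low retention as evidence that women left the study. Neither reading would be safe.

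**Working it through.** The plan gives no figure of its own on this point, so the check is mainly a reading of the rule, followed by its arithmetic at the planned arm size.

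**1. The rule as a classification.** Take lifestyle-arm women who do not ask to leave and who attend both assessments. Withdrawals then sorts them as follows.

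| Logging continues | Behaviour changed | Status | Data used |
|---|---|---|---|
| Yes | Yes | Retained | Yes |
| Yes | No | Retained | Yes |
| No | Yes | Withdrawn | No |
| No | No | Withdrawn | No |

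Status follows the first column and is unaffected by the second.

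**2. Does the compliance measure fill the gap?** Of the two sources named under Feasibility outcomes, session attendance does not apply to this arm, which leaves the recorded daily activity. Allocation follows the baseline assessments, and app tracking is described only for women allocated to this arm. I infer from this that no app value from before allocation is planned; the article does not say so directly. Without one, the record shows the level of activity and its course over the 12 weeks, but by itself it does not show change from before the intervention. Entry is limited on structured exercise only (more than 150 min/week excludes), so everyday activity at entry may vary between women.

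**3. What does measure change?** The IPAQ, given before and after in all three arms, covers both lifestyle activity and sitting time. The article lists it under Secondary outcomes and does not link it to compliance.

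**4. Size at the planned arm.** Arm size from Data analysis: 51 / 3 = 17.

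- If all 17 women log and none changes, retention is 17/17 = 100%. The exact (Clopper-Pearson) lower 95% limit is 0.025^(1/17) = 0.805, so the interval is 80.5% to 100%. Uptake in the same women is 0/17, with upper limit 1 − 0.805 = 0.195, or 19.5%.
- If k women stop logging but attend the post-intervention assessment, and no one else is lost, attrition reads k/17 and the analysed arm is 17 − k. The article gives no value for k, so the values below are assumed.

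| k (assumed) | Attrition as written | Women analysed | Women with both assessments |
|---|---|---|---|
| 1 | 1/17 = 5.9% | 16 | 17 |
| 3 | 3/17 = 17.6% | 14 | 17 |
| 5 | 5/17 = 29.4% | 12 | 17 |

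**The case against.** The strongest reply is that retention and compliance are different outcomes and the article keeps them apart. Keeping non-changers as retained is normal, and making behaviour change a condition of retention would introduce selection. The exercise arm works in a similar way, since attendance rather than achieved intensity keeps a woman in. All of this stands. The difference is that attending a supervised session is receipt of the exercise intervention, whereas logging is not receipt of the lifestyle one. The reply also leaves untouched the women who stop logging and are discarded.

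A reader might infer that uptake would never be shown. The documents do not support that. The IPAQ is collected before and after in every arm, weekly telephone contact asks about progress, and interviews explore acceptability. If no woman became more active, the planned IPAQ comparison is there to show it.

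A reader might also infer that logging is the sole condition for staying in, or that the log certainly begins after allocation. The first is wrong: request to leave and loss to follow-up also end participation, and analysis requires both assessments. The second is only an inference, because the apps are often already on the phone and may hold earlier data. A 12-week record can also show a trend within a woman from early to late weeks, although it would miss a change made at the start.

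Finally, this is a condensed article, and a numerical cut-off for compliance may properly sit in the full protocol or SAP. I make no point of its absence. The withdrawal rule and its consequence for the analysis are stated in the text.

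**Conclusion.** The point holds in a limited form. The only withdrawal criterion specific to the lifestyle arm is stopping app logging, and data from withdrawn women are not used. The arm's attrition figure and analysis set therefore describe adherence to self-monitoring. They do not describe adherence to increasing activity and reducing sedentary time. The measure that could show uptake against a baseline is already collected but is not connected to compliance.

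Each woman who stops logging but is assessed moves attrition by 5.9 percentage points and removes one of 17 from the analysis. Full retention is compatible with no uptake. How many women would stop logging is unknown, so the overall effect cannot be stated in advance.

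The conclusion about the withdrawal rule rests on its wording alone. The conclusion about the app record also assumes that no data from before allocation would be used. The change is worth making because the rule feeds a primary feasibility outcome and the correction is cheap.

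**What to change.** **Withdrawals.** Treat stopped logging as non-adherence to self-monitoring rather than as withdrawal. Keep in the analysis every lifestyle-arm woman who has baseline and post-intervention assessments, whether or not she logged and whether or not she changed. Withdrawal in this arm then rests on the two general grounds.

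**Feasibility outcomes.** For the lifestyle arm, report two things separately:

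- (a) adherence to self-monitoring, as days with app data;
- (b) uptake of the intervention, as the mean IPAQ change from baseline to 12 weeks in lifestyle activity and in sitting time, each with a 95% CI and read against the control arm. Where the phone already holds app data from before allocation, use them as a supplement.

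I would not report the proportion of women who increased. With symmetric error in a self-reported measure, about half of those with no true change would be counted as increasers.

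**Cost.** Wording changes in two sections and one added summary of data already collected, with no extra visits or participants. The IPAQ is self-reported, stored app history will exist for only some women, and reported uptake may look less favourable than retention does now.

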### Eligibility criteria

Participants eligible for the trial must meet the below inclusion criteria as follows:
i)Women diagnosed with PCOS according to the Rotterdam criteria 2003, National Institute of Health (NIH) 1990 criteria or Androgen Excess and Polycystic Ovary Syndrome (AE-PCOS) Society 2006 criteriaii)Have experienced menarche (their first menstrual bleeding) and be at least 18 years of ageiii)Are English speakingiv)Are physically able to perform exercise

Exclusion criteria include:
i)Post-menopausal statusii)Are smokersiii)Are undertaking regular structured exercise defined as > 150 min/weekiv)If taking metformin, have been taking it for < 3 monthsv)Are taking the oral contraceptive pill (OCP) or have taken it in the last monthvi)Have any medical condition that may be responsible for the symptoms of PCOS, such as congenital hyperplasia, androgen-secreting tumour, hyperprolactinemia, or Cushing’s syndromevii)Have current, clinically defined CVD or a history of cardiac events

Participants will be advised that commencement of any of the above-mentioned medications during the trial is a contraindication and they will be withdrawn from the trial.

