### Interview and qualitative methods

After trial completion, four participants from each group, as well as drop-outs, will be offered the opportunity to complete a semi-structured interview either in person or over the telephone with a member of the research team. All interviews will be recorded with an audio recording device and then transcribed verbatim. The interview will explore their opinions and experiences of the intervention, and factors that may be a barrier or facilitator to physical activity in the future. It will also assess the acceptability of the exercise intervention and study procedures, to refine the design and delivery of the exercise programme for the RCT, and will last approximately 45 min.

Interviews will allow the exploration of participant’s motivations, attitudes and experience in detail and within their personal frame of reference. This will be useful because of the wide-ranging symptoms of PCOS, which may affect individuals in a variety of ways that are not necessarily uniform across all participants. Transcripts will be analysed using thematic analysis [22]. Thematic analysis is an inductive method for identifying, analysing and reporting patterns within data. As such, it allows for a great deal of flexibility in analysing qualitative data because it is independent of theory and epistemology; rather, it can be applied across a range of theoretical approaches [22]. This allows for themes and patterns to be identified by the researcher without trying to fit it into a pre-existing coding frame, and is therefore considered to be data-driven and accessible [22].

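### The completers-only rule, with stopping triggers only in the two active arms, breaks the randomised comparison and is not reconciled with the feasibility outcomes

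*Protocol article*

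**What the plan says.** The analysis set is fixed in the Withdrawals section: "Data from withdrawn participants will not be used; only data from participants who completed the intervention" and both assessments enter the analysis.

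The same section defines who is withdrawn:

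- Any arm: "A participant will be considered to be withdrawn if they request to leave the trial or they are lost to follow-up".
- Exercise arm: "participants will be considered as withdrawn if they no longer attend the supervised exercise sessions".
- Lifestyle arm: "in the lifestyle physical activity group if they no longer monitor daily physical activity through the fitness application".
- Control arm: no further trigger. The control group has no intervention that could be stopped.

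The Eligibility criteria section adds a trigger for all arms: "commencement of any of the above-mentioned medications during the trial is a contraindication and they will be withdrawn from the trial".

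The Data analysis section compares groups by mixed ANOVA with time within and group between subjects. It names no analysis of all randomised women and no sensitivity analysis.

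Other sections rely on the women who leave. Feasibility outcomes, which are primary, define attrition as discontinuation plus loss to follow-up, and state: "Compliance will be monitored by session attendance and monitoring the data from recorded daily physical activity, with examination of reasons for drop-out or non-compliance". The interview section says that "four participants from each group, as well as drop-outs, will be offered the opportunity to complete a semi-structured interview". The aims at the end of the Background include retention, interviews with dropouts, and an SD for oxidised LDL to size the later trial.

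**The concern.** Exclusion depends on behaviour after allocation, and two of its triggers can operate only in the active arms. A woman who stops using the app but could attend her week-12 visit is removed, while a control who changes her habits in any way is kept. The ANOVA then sets persistent active-arm women against nearly all controls. If women who stop would have had worse results, the active arms look better with no treatment effect at all. The Discussion says that effect sizes from this study will plan the full-scale trial, so the distortion would carry forward.

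The rule also discards information already in hand. Envelopes are offered after baseline assessment, so every randomised woman should have baseline blood for the oxidised LDL SD.

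Finally, the exclusion sentence is not limited to the clinical outcomes. Taken at its word, it clashes with the primary outcomes.

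**Working it through.** **Plan's own figure.** 3 groups × 17 = 51, as stated. No power calculation, SD or drop-out rate is given, so everything on loss below is assumed.

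**Numbers or selection?** The plan cites a rule of thumb of at least 30 women. Since 51 − 30 = 21, the completer set stays at 30 or more up to a loss of 21/51 = 41%. The main harm is selection, not size.

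**Spurious difference with no true effect.** Assumptions: 17 per arm; the 5 women in one active arm with the highest drop-out propensity are lost and no control is; propensity has correlation r with the week-12 value (higher is worse); baseline and week-12 values have correlation 0.5 and equal SD; propensity acts through the week-12 value.

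- The top 5 of 17 standard normal values average 1.113 (simulated). The 12 kept therefore average −1.113 × 5/12 = −0.464.
- Bias in week-12 means = r × 0.464.
- The same women's baseline mean shifts by half as much (0.5 × r × 0.464), so bias in change = r × 0.464 × (1 − 0.5).

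| r | Week-12 means (SD) | Change (SD) |
|---|---|---|
| 0.2 | 0.093 | 0.046 |
| 0.4 | 0.186 | 0.093 |
| 0.6 | 0.278 | 0.139 |

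The change column corresponds to the planned group-by-time contrast. Direct simulation of 20,000 trials agreed (0.044, 0.094 and 0.139 in change).

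More generally, bias = (share excluded in active arm − share excluded in control) × D, where D is the completer-minus-excluded difference in SD units. With 20% against 5% excluded and D = 0.5, this is 0.15 × 0.5 = 0.075 SD. With 40% against 10% and D = 1.0, it is 0.30 SD.

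**SD of the week-12 outcome.** The propensity variance among the 12 kept is 0.522 (simulated). The outcome variance in the depleted arm is therefore v = 1 − r²(1 − 0.522).

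- Depleted arm alone: SD ratio 0.990, 0.961 and 0.910 for r = 0.2, 0.4 and 0.6, which is 1% to 9% too small.
- Pooled, one arm depleted (degrees of freedom 11, 16, 16): √[(11v + 32)/43] = 0.998, 0.990, 0.978, or about 0.2% to 2% too small (the separate simulation put the lower end at 0.3%).
- Pooled, both active arms depleted: √[(22v + 16)/38] = 0.995, 0.978, 0.949, or up to about 5% too small.

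**Precision of the SD.** The 95% limits are √(df/χ²). With all 51 baselines (df 50) they are 0.84 to 1.24 times the estimate. With 20% lost (41 women, pooled df 38) they are 0.82 to 1.29 times.

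**Feasibility rates.** If these too were restricted to completers, attrition would be 0/n = 0% and assessment completion 100% by construction. With all randomised women as denominator, 10 losses would give 10/51 = 19.6% (95% CI 9.8% to 33.1%).

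**The case against.** The best defence is that the Withdrawals sentence was meant only for the pre/post outcome analysis, since it speaks of both assessments. The feasibility section plainly plans to count discontinuation and examine reasons for leaving, and the interview section invites drop-outs. This largely stands. A reader might infer that the rule certainly destroys the data behind the primary outcomes, or that compliance will be computed in adherent women only. The documents do not support that: no section restricts compliance to completers, and withdrawals can be counted without outcome data. What remains is a contradiction between sections that nobody has resolved.

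A reader might also infer that every non-adherent woman is dropped. The trigger is stopping attendance or logging; a woman who attends irregularly is not clearly excluded.

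The effects can be overstated as well. The 0.09 to 0.28 SD range applies to week-12 means, and the planned contrast shows about half of it. The SD shrinkage of up to 9% belongs to the depleted arm alone. The pooled figure is small beside the sampling error of an SD from about 50 women, so the case on the SD aim is mainly that usable baseline data are thrown away.

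Lastly, the clinical outcomes are secondary and the Data analysis section warns of low power. That lowers the stakes, but a warning about power does not cover selection bias.

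**Conclusion.** The concern holds for the outcome analysis. As written, the plan compares women selected on behaviour after randomisation, through triggers that differ by arm, and gives no analysis of the groups as allocated. On the assumed inputs the spurious effect is about 0.05 to 0.14 SD in change, with a pooled SD at most about 2% too small (about 5% with both active arms depleted). These figures rest on an assumed loss of 5 of 17, a correlation of 0.5 between visits, and drop-out tied to the week-12 value; other mechanisms would give other sizes. The arm-dependent exclusion itself does not depend on those assumptions.

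For the feasibility outcomes the finding is narrower: the Withdrawals section and the aims, feasibility and interview sections cannot all be followed literally and must be reconciled.

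**What to change.** In the Withdrawals section, replace the exclusion sentence with four statements:

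1. All randomised women are analysed in their allocated group using every available measurement, including all baseline oxidised LDL values for the SD.
2. Stopping sessions or the app does not by itself remove a woman's data or her already scheduled week-12 assessment.
3. Data are removed only when a woman withdraws them.
4. Feasibility rates use all randomised women as denominator.

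A completers-only analysis may stay as a labelled sensitivity analysis. For women withdrawn under the medication rule in the Eligibility criteria, state only how data already collected are handled; the rule itself is for the sponsor.

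The cost is small. The sample size stays at 51 and no visit is added. There is slightly more analysis work, and some week-12 values will be missing. A standard mixed ANOVA drops women without both values, so the plan needs to say how incomplete pairs are handled.
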